## Abstract

**Background:**

The purpose of this trial is to evaluate the effectiveness and safety of electroacupuncture in the treatment of acute decompensated heart failure compared with sham electroacupuncture.

**Methods:**

This protocol is for a randomized, sham controlled, patient- and assessor-blinded, parallel group, single center clinical trial that can overcome the limitations of previous trials examining acupuncture and heart failure. Forty-four acute decompensated heart failure patients admitted to the cardiology ward will be randomly assigned into the electroacupuncture treatment group (*n* = 22) or the sham electroacupuncture control group (*n* = 22). Participants will receive electroacupuncture treatment for 5 days of their hospital stay. The primary outcome of this study is the difference in total diuretic dose between the two groups during hospitalization. On the day of discharge, follow-up heart rate variability, routine blood tests, cardiac biomarkers, high-sensitivity C-reactive protein (hs-CRP) level, and N-terminal pro b-type natriuretic peptide (NT-pro BNP) level will be assessed. Four weeks after discharge, hs-CRP, NT-pro BNP, heart failure symptoms, quality of life, and a pattern identification questionnaire will be used for follow-up analysis. Six months after discharge, major cardiac adverse events and cardiac function measured by echocardiography will be assessed. Adverse events will be recorded during every visit.

**Discussion:**

The result of this clinical trial will offer evidence of the effectiveness and safety of electroacupuncture for acute decompensated heart failure.

**Trial registration:**

Clinical Research Information Service: KCT0002249.

## Background

Heart failure (HF) is defined as *“a complex clinical syndrome that can result from any structural or functional cardiac disorder that impairs the ability of the ventricle to fill or eject blood.”* according to the American Heart Association guidelines [1]. Conventional Western medical treatment for HF includes beta blockers, angiotensin-converting enzyme inhibitors (or angiotensin receptor blockers), and diuretics [2]. The overall prevalence of HF is estimated to be from 1% to 12%; it is known that there are more than 23 million HF patients worldwide [3]. Therapeutic improvement for HF and an aging population has led to increased prevalence of HF. In spite of therapeutic developments for HF, mortality is still high [4]. Due to chronic clinical course and frequent readmission, the burden of HF is increasing [3]. Further, despite therapeutic improvements, the 5-year survival rate of HF is 50%, and the 10-yr survival rate is only 10% [5, 6]. Therefore, another treatment approach is needed, and traditional East Asian therapies such as acupuncture and herbal medicine may be considered in this regard [7–10].

One of the important pathophysiologies of HF is autonomic nervous system (ANS) imbalance [11]. It is known that heart rate variability (HRV) reflects ANS status [12]. HRV predicts the mortality and prognosis of HF patients [13, 14]. Acupuncture is known to modify the ANS tone [12], and it is already known that several acupuncture points, such as PC6 and ST36, affect ANS tone through regulation of sympathetic outflow from rostral ventral medulla in the central autonomic pathway [15, 16]. Several acupuncture clinical trials have been conducted [17–23]. However, according to a recent systematic review of acupuncture treatment for HF, the studies had several limitations and the methodological quality was relatively low [24]. The review suggested several implications for future clinical trials. It also suggested that several important outcomes should be included in future acupuncture clinical trials of HF. Clinical outcome variables such as mortality, major adverse cardiac events (MACE), and the New York Heart Association (NYHA) Functional Classification should be investigated. Other objective surrogate outcomes such as cardiac biomarkers, N-terminal pro b-type natriuretic peptide (NT-pro BNP), and cardiac function measured by echocardiography should also be included. Additionally, total diuretic doses for each group during hospitalization should be reported, as excessive diuretics cause an electrolyte imbalance that increases the risk of a cardiovascular event. In terms of intervention, most HF acupuncture experimental studies used electroacupuncture, but only one clinical trial adopted electroacupuncture; the review suggested usage of electroacupuncture with a 2-Hz frequency. For the clinical trial process, the review suggested a long-term follow-up duration to assess the long-term effects of acupuncture treatment [24].

According to the implications for future clinical trials of the previous review, our study team planned an electroacupuncture clinical trial for acute decompensated HF patients that could overcome previous limitations. First, our primary outcome was the total diuretic dose administered during hospitalization, which has been recorded in several acute HF clinical trials [25–28]. As acupuncture treatment is an adjunctive treatment in cases of HF, our research team concluded that reducing the total dose and the adverse effects of the diuretics through acupuncture treatment is meaningful. Second, we included several important outcomes, such as mortality, MACE, NYHA Functional Classification, cardiac biomarkers, NT-pro BNP, and cardiac function measured by echocardiography. Third, we adapted the electroacupuncture protocol. In addition, we adapted a Park Sham Device (PSD; Acuprime, Exeter, UK), a validated sham acupuncture device [29], to maintain blindness and non-biased measurement of subjective outcomes. Last, we will follow the participants until 6 months after discharge to assess the long-term effects of acupuncture treatment in acute HF.

## Methods/design

Our protocol was written in accordance with Standard Protocol Items: Recommendations for Interventional Trials (SPIRIT) [30] which was aim to improve the quality of clinical trial.

### Objectives

The objective of this trial is to determine the effectiveness and safety of adjunctive electroacupuncture treatment administered in conjunction with conventional treatments in cases of acute decompensated HF patients, as measured by diuretic dose, electrolyte imbalance, renal function, HF symptoms, quality of life, cardiac biomarkers, NT-pro BNP, high-sensitivity C-reactive protein (hs-CRP), cardiac function, HRV, and MACE compared with sham electroacupuncture.

### Trial design and study setting

This study is a randomized, sham controlled, parallel group, patient- and assessor-blinded, single center clinical trial.

### Recruitment period and method

We will recruit participants who are admitted to the cardiology ward of Kyung Hee Medical Center (KHMC) for treatment of acute HF. Attending physicians (Western medicine cardiologists) will check the inclusion criteria and inform patients or guardians about the acupuncture clinical trial. If the patient or guardian agrees to participate in the trial, written informed consent will be obtained by attending physicians. Recruitment is expected to continue from March 2016 until May 2019. We will not use other advertising methods such as a homepage, bulletin boards, or mass media.

### Type of participants: inclusion and exclusion criteria

#### Inclusion criteria

Participants who satisfy the following criteria will be recruited:Over 40 years of age, with written informed consent.Acute HF patient presenting with dyspnea related to cardiogenic pulmonary edema and in need of diuretic treatment.Systolic blood pressure > 95 mmHg at admission.B-type natriuretic peptide (BNP) > 150 pg/mL or NT-pro BNP > 600 pg/mL.

#### Exclusion criteria

Participants who have any of the following conditions will be excluded from the study:Body temperature > 38.0 °C or in need of intravenous antibiotic treatment due to acute inflammation or sepsis.K < 3.5 mEq/L (patients with potassium levels of 3.0 to approximately 3.5 mEq/L may be admitted if they agree to receive potassium treatment).Currently take or plan to take vasopressors, inotropics, have an intra-aortic balloon pump, extracorporeal membrane oxygenation, or endotracheal intubation.Require a heart transplantPresent with possible acute coronary syndrome within 2 weeksAcute HF related to significant arrhythmia (ventricular fibrillation, ventricular tachycardia, atrial fibrillation, atrial flutter, complete AV block)Acute HF related to acute myocarditis, hypertrophic cardiomyopathy, restrictive cardiomyopathy, constrictive cardiomyopathyIn need of or currently receiving hemodialysis or peritoneal dialysisAbnormal liver function (total bilirubin >3 mg/dL, albumin <2.8 mg/dL)In need of a blood transfusion (hemoglobin <8 g/dL or hematocrit <25%)Chronic obstructive pulmonary diseaseCurrently undergoing treatment for or with a history of malignant tumorPregnant or breast-feedingUnable to follow up (outpatient clinic) for more than 6 monthsCurrently participating in another clinical trial.

### Randomization and allocation concealment

A random number table will be generated with the computerized random number generator Package randomizeR (R Core Team (2013), R Foundation for Statistical Computing, Vienna, Austria). The random number table will be prepared by an independent researcher. The random number file will be protected by a password. Allocation will be concealed until informed consent is obtained. If the participants satisfy the inclusion criteria and sign informed consent, the Korean Medicine Doctor who will conduct the acupuncture treatment will be informed of the group allocation.

### Blinding

The clinical research coordinator, assessor, attending physician, and participants will be blinded. Due to characteristics of the acupuncture clinical trial, the acupuncture practitioner cannot be blinded. To blind participants, we will use PSD regardless of group allocation. PSD is a validated sham device for acupuncture trials [29]. With the exception of PSD, other factors such as doctor-patient relationship, the clinical trial process, and the environment will be identical so that participants cannot guess their allocated group. The clinical research coordinator and the attending physician (a Western medicine cardiologist) will be blinded until completion of the study. The assessor will also be blinded. To maintain blinding, the assessor and participants will be educated according to the Standard Operation Procedure (SOP). We will notify allocated group to participants if serious adverse events occurs according to SOP.

To identify blinding success, direct assessment of blinding by the blinding index (BI) [31, 32] and indirect assessment by a credibility test [33] and acupuncture expectancy scale [34] will be conducted on Day 1 and Day 5 of the clinical trial. In the BI, patients will be required to select one of the following three statements: “I think I belong to the treatment intervention group”, “I think I belong to the control intervention group”, or “I do not know”. On the acupuncture expectancy scale, patients will answer the following four questions using a five-point Likert scale: *“ 1) My illness will improve a lot, 2) I will be able to cope with my illness better 3) The symptoms of my illness will disapper 4) My energy level will increase”*. In the credibility test, patients will answer the following four questions using a seven-point Likert scale:*“1) How confident do you feel that this treatment can alleviate your acute HF?”; “2) How confident would you be in recommending this treatment to a friend who suffered from a similar complaint?”; “ 3) How logical does this treatment seem to you?”; “ 4) In your opinion, how successful may this treatment be in alleviating other complaints?”*

### Intervention

#### Study flow

If the participants voluntarily sign informed consent during admission to the cardiology ward, participants will be screened according to inclusion and exclusion criteria on the screening day. After the subject fulfills the criteria, the basic characteristics and prognostic factors of each participant will be evaluated. The subjects will be randomized into an intervention and a control group with a 1:1 allocation ratio on the same day; the screening day and Day 1 will usually be the same day. From Day 1 to Day 5, the participants will receive electroacupuncture treatment or sham electroacupuncture treatment once a day for consecutive 5 days according to their allocated group. After discharge, participants will visit KHMC three times. Visit (V1) will be 7 days after discharge. Visit 2 (V2) will be 28 days after discharge. Visit 3 (V3) will be 180 days after discharge. On the day discharge (Day 5) and V2, blood tests, quality of life (QOL), and a pattern identification questionnaire according to traditional East Asian medicine (TEAM) theory will be evaluated. On V3, cardiac function and MACE will be evaluated by echocardiography (Table 1). Participants will be withdrawn from the study if they 1) re-admit to hospital related to cardiac or kidney dysfunction 2) withdraw of consent by participants 3) worsening cardiac function 4) the principle investigator judged that participants can not continue the research.

**Table 1 Tab1:** Study schedule

Study period	Screening visit	Acupuncture treatment period					Follow-up period		
Visit	Screening	D1	D2	D3	D4	D5	V1	V2	V3
Informed consent	X								
Demographics and history collection	X								
Inclusion and exclusion criteria	X								
Randomization		X							
Physical examination and vital signs check	X	X	X	X	X	X	X	X	X
Body weight	X	X	X	X	X	X	X	X	X
Symptoms check (NYHA Functional Class)	X	X	X	X	X	X	X	X	X
Adverse events	X	X	X	X	X	X	X	X	X
Concomitant medication check	X	X	X	X	X	X	X	X	X
Routine blood test^a^	X		X			X		X	X
NT-pro BNP, hs-CRP	X					X		X	
Cardiac biomarkers^b^		X				X			
Cardiac function (echocardiography)	X								X
Electrocardiogram and HRV		X				X			
QOL and symptom questionnaire^c^		X						X	
Credibility and AES		X				X			
Blinding test		X				X			
Acupuncture treatment		X	X	X	X	X			

*Abbreviations*: *AES* acupuncture expectancy scale, *D5* date of discharge, hs-*CRP* high-sensitivity C-reactive protein, *HRV* heart rate variability, *NT-pro BNP* N-terminal pro b-type natriuretic peptide, *NYHA* New York Heart Association, *QOL* quality of life, *V1* 7 days post-discharge ±5 days, *V2* 28 days post-discharge ±7 days, *V3* 180-days post discharge ±14 days

^a^Routine blood test: complete blood cell count and different counts (CBC, DC), blood urea nitrogen (BUN), creatinine, electrolyte (Na, K, Cl), total bilirubin, glucose, total protein, albumin, aspartate aminotransferase (AST), alanine aminotransferase (ALT)

^b^Cardiac biomarkers: atrial natriuretic peptide (ANP), ST2, catecholamine, vasoactive intestinal peptide (VIP), interleukin 6 (IL-6), vascular adhesion protein-1 (VAP-1)

^c^QOL and symptom questionnaire: EuroQol five dimensions questionnaire (EQ-5D), Minnesota Living with Heart Failure Questionnaire (MLHFQ), pattern identification questionnaire according traditional East Asian medicine theory

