#### Cardiac function

Echocardiography is a helpful, non-invasive assessment tool of ventricular function and hemodynamics in HF patients. Ejection fraction (%), the ratio between early mitral inflow velocity and mitral annular early diastolic velocity (E/e’ ratio), left ventricular fractional shortening (%), left ventricular end diastolic diameter (mm), and left ventricular end systolic diameter (mm) will be evaluated by echocardiography to assess cardiac function. Follow-up echocardiography will be assessed 180 days after discharge. The changes in value from the baseline between the two groups will be compared.

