#### MACE

Mortality due to heart and kidney problems and the readmission rate between the two groups will be compared until 180 days after discharge.

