### Statistical analysis

The primary outcome of our study is the cumulative amount of diuretic administered to each group. After a normality test, the total amount will be compared by an independent *t*-test (parametric) or a Mann-Whitney U test (non-parametric) according to the normality of the data. If the baseline characteristic is significantly different between the two groups, an analysis of covariance (ANCOVA) will be used to adjust the baseline difference. In baseline characteristics and secondary outcome analysis, binary outcomes will be compared by a chi-square test or Fisher’s exact test. Continuous outcomes will be compared by an independent *t*-test (parametric) or Mann-Whitney U test (non-parametric). MACE will be also be analyzed using the survival analysis method. Statistical analysis will be performed using the R package by a blinded statistician. A 5% significance level will be used. Missing values will be replaced by the last observation carried forward method. If there are more than 20% of drop out participants, sensitivity analysis will be conducted including the data.

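### Withdrawal on cardiac or renal readmission, or on worsening cardiac function, ends observation of patients because they had a 180-day secondary outcome

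*Protocol article*

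**What the plan says.** The protocol article, Study flow, gives four grounds for leaving the study. The first is readmission: "Participants will be withdrawn from the study if they 1) re-admit to hospital related to cardiac or kidney dysfunction". The second is withdrawal of consent. The other two read "3) worsening cardiac function 4) the principle investigator judged that participants can not continue the research". No threshold or time window is attached to worsening cardiac function.

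Two of these grounds are also outcomes. Under MACE: "Mortality due to heart and kidney problems and the readmission rate between the two groups will be compared until 180 days after discharge". Under Cardiac function: "Follow-up echocardiography will be assessed 180 days after discharge". Table 1 shows that the only other echocardiogram is at screening.

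On treatment, Study flow says that "the participants will receive electroacupuncture treatment or sham electroacupuncture treatment once a day for consecutive 5 days", and the article treats Day 5 as the day of discharge.

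Under Statistical analysis: "MACE will be also be analyzed using the survival analysis method". Also "Missing values will be replaced by the last observation carried forward method", and "If there are more than 20% of drop out participants, sensitivity analysis will be conducted including the data".

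Nowhere does the article say that a withdrawn participant is still followed for events, vital status or the V3 visit.

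**The concern.** A rule that ends a patient's participation can serve to stop treatment. Here no study treatment remains after discharge, so a readmission rule can only stop data collection. It does so for patients who have just had the kind of event that the 180-day follow-up is meant to record. The Background gives long-term follow-up to six months as one of the reasons for the trial, and describes readmission in heart failure as frequent, so the trigger is unlikely to be rare.

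The secondary outcomes are at stake. Loss of follow-up would depend on outcome and fall on the sickest patients. A survival analysis of cardiac or renal death would censor people at the point where their risk has probably risen. The change in echocardiographic function would be computed with a substituted value in the patients who did worst.

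**Working it through.** **The plan's own figure.** The only stated number that touches this point is the dropout allowance. From Sample size calculation:

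- difference = 256 − 223 = 33 mg
- pooled SD = √((26² + 39²)/2) = √1098.5 = 33.14
- d = 33/33.14 = 0.996

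A two-sided t-test at 0.05 (noncentral t) has power 0.778 with 16 per group and 0.804 with 17, so 17 is reproduced. Then 17/(1 − 0.20) = 21.25, rounded up to 22 per group, 44 in total. These figures are correct. They concern the primary comparison only.

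**What the rule removes and what it leaves**

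| Item | Where planned | After withdrawal on readmission |
|---|---|---|
| Cumulative diuretic dose | Admission to discharge | Complete |
| First readmission | MACE, to 180 days | Can be counted, since it is the trigger |
| Repeat readmission | MACE, to 180 days | Lost |
| Later cardiac or renal death | MACE, to 180 days | Lost; censored at withdrawal |
| Echocardiogram | Screening and V3 only | V3 lost |
| NYHA class, routine blood tests | Several visits, including V3 | V3 lost |
| Questionnaires, NT-pro BNP, hs-CRP | Last measured at V2 | Lost only if withdrawn before V2 |

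**How many.** The documents give no readmission rate, so the rate r is assumed over a range, as is the share q of readmitted patients who later die of a cardiac or renal cause. Withdrawn = 44 × r; left for V3 = 44 × (1 − r); deaths unobserved = 44 × r × q. Other losses are ignored.

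| r | Withdrawn | Left for V3 echo | Deaths unobserved, q = 10% | q = 30% |
|---|---|---|---|---|
| 10% | 4.4 | 39.6 | 0.4 | 1.3 |
| 20% | 8.8 | 35.2 | 0.9 | 2.6 |
| 30% | 13.2 | 30.8 | 1.3 | 4.0 |
| 40% | 17.6 | 26.4 | 1.8 | 5.3 |

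**Effect of LOCF on the echocardiogram (assumed values).** Let patients not readmitted gain 5 ejection-fraction points. Let readmitted patients do 10 points worse, that is −5. Let readmission be 20% in the active arm and 40% in the sham arm.

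- Truth: active 0.8 × 5 + 0.2 × (−5) = 3; sham 0.6 × 5 + 0.4 × (−5) = 1; difference 2.0.
- LOCF from screening (change set to 0): active 0.8 × 5 = 4; sham 0.6 × 5 = 3; difference 1.0.
- Completers only: 5 − 5 = 0.

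The size depends on the assumptions. If readmitted patients do only 5 points worse (change 0), truth and LOCF both give 1.0. If they still improve somewhat, LOCF overstates the difference. With equal readmission rates in this simple model, both differences are zero.

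**The case against.** The strongest reply is that the rule does less damage than it appears to, and four parts of that reply stand.

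- **The readmission itself is not lost.** A reader might infer that an arm with more readmissions would come to look like the other. For a time-to-first-event analysis that is not so: the trigger is known and can be counted.
- **The primary outcome is untouched by readmission.** The diuretic total closes at discharge. A reader might infer that these withdrawals use up the 20% dropout allowance. They do not: that allowance inflates 17 to 22 for the primary comparison, and a patient withdrawn after discharge already has complete primary data. The 20% under Statistical analysis is a trigger for a sensitivity analysis, not a limit.
- **V3 carries less than one might assume.** Table 1 has no questionnaires and no NT-pro BNP at V3, so those are lost only when withdrawal comes before V2.
- **The plan does not specify a completer analysis.** The zero in the example above belongs to an analysis that the article does not propose. The stated LOCF attenuates the difference in that example and does not erase it.

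It could also be said that an article condenses a fuller protocol. That does not help here, because the withdrawal rule is stated outright and conflicts with outcomes stated in the same document. An analysis plan cannot restore data that were never collected. Nor does the 20% trigger help, since it looks at how much is missing and not at why.

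**Conclusion.** The rule is wrong as written. Two withdrawal grounds overlap with the 180-day outcomes, and after Day 5 they can only end observation. The losses are later cardiac or renal deaths, repeat readmissions, the V3 measurements and, for early withdrawals, the V2 measures.

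On assumed readmission of 10% to 40%, about 4 to 18 of 44 patients would have no V3 echocardiogram. Over the ranges tabulated, roughly 0.4 to 5.3 deaths would go unobserved. Both ranges rest on assumptions, not on figures in the article. For a patient withdrawn because of worsening, LOCF records no change. The resulting bias in the group difference can be nil or run in either direction, depending on readmission by arm and on how readmitted patients fare.

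A reader might infer that the primary result is compromised. The documents do not support that for readmission. The primary outcome is exposed only if the worsening criterion, which has no time window, is applied during the stay. That could cut short the recorded diuretic total of a deteriorating patient.

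**What to change.** In Study flow, remove cardiac or renal readmission and worsening cardiac function as reasons for leaving the study, and state that both are recorded as outcomes. State that all randomised participants are followed for MACE, vital status and V3 echocardiography to day 180 after discharge, unless they withdraw consent or die. Keep any rule on stopping acupuncture sessions separate from leaving the study; no clinical rule is proposed here.

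The cost is a short amendment and some extra effort to follow readmitted patients. The V2 and V3 visits are already in the schedule. The article does not say where readmissions take place, so the effort of tracing patients admitted elsewhere cannot be judged from it. Recruitment is under way, and follow-up that is not done cannot be recovered at the analysis stage, so the change should be made early.
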